**Figure 2 F2:**
[figure not shown]
**Diagram of the hypothesised relationships between experimental variables.** This figure illustrates direct **(A)** and meditational **(B** and **C)** relationships between experimental (e.g. autonomous motivation) and dependant variables (e.g. implementation).

We will deal with missing data using full-information-maximum-likelihood estimation (FIML). Traditional approaches to missing data (*e*.*g*., list-wise or pair-wise deletion) can lead to considerable bias in parameter estimates. In contrast FIML provides a superior approach to dealing with missing data that uses all the available information for parameter estimation [54].

Standard multiple regression analysis will test for predictors of transfer. In terms of knowledge transfer related to the new workplace practices, we will compare current findings with the pre-post effect sizes extracted from the previous work conducted by the research team [51]. In that study, effect sizes were moderate based on Cohen’s criteria (STARS = 0.25, RKI = 0.52) with a sample size of 75. Given the additional components of this intervention we are expecting slightly higher effect sizes. Data collected in the CRM-VQ will enable comparison of these predictors with participant self-reported implementation of the new work practices.

Work-sampling audits will also be used as an objective measure of transfer. We are anticipating a sample size of 200 at time point one, but have allowed for a more modest sample size of 100 in calculating power analyses. In our previous study, we found 37% of people transferred training. With this information we are able to estimate the percentage of people who need to demonstrate transferred practices in work samples in order to show a significant increase in the proportions between the former and present studies. Using Z test for proportions we have calculated that we need at least 48 out of the 100 participants to obtain a significant difference at p<0.01 to detect a 10% increase in transfer. We believe this difference is very achievable with the addition of the values-focused interventions.

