### Data collection and handling

The study will last 18 months with data collection at multiple times points. Primary data comprises a questionnaire battery completed by participants at five time points throughout the intervention (specific measures are outlined below). Data is also collected from coaches and recipients’ at each monthly coaching session to assess adherence to the GROW framework, integrity to experimental condition, and elements of the coaching alliance. In addition to self-reported measures of implementation, the study uses objective measures of transfer (also outlined below).

Data collection handling is in accordance with the procedures specified in the ethics approval obtained from the Human Research Ethics Committee at the University of Wollongong (HE09/221). A prime focus is on maintaining confidentiality of participants, which is promoted by the use of a unique self-generated identifier established at the first data collection point and re-used at subsequent collections. Additionally, because the research focuses on work-related variables and is being conducted in a work setting, individual data is forwarded to the research team directly (*i*.*e*., handed personally in sealed envelopes when on-site). This is to reduce possible biased responding and staff concerns that their individual information could be seen by superiors or other personnel within their organisation.

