### Measures and data

The battery of measures will also include measures of intention to leave [48] job satisfaction [49], and burnout [50]. This additional data will be utilised by the research team to explore another set of hypotheses distinct from those being investigated here. Questionnaires pertaining to the outlined hypotheses are as follows.

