## Discussion

### Anticipated challenges

There are a number of challenges to carrying out this project due to the applied and organisational nature of this research. The schedule of intervention needs to meet standards of feasibility and pragmatism for the partner organisations, which are contributing significantly in terms of in-kind and cash contributions. Such challenges include the need to roll-out intervention components at a rate that enables partners (who are service providers) to equip and up-skill staff and accommodate the needs of new staff, which will at times put pressure on the capacity of the research team to deliver the intervention. Additionally, the need for interventions (particularly coaching) be practical and manageable has influenced the choice of methodology to be employed (*e*.*g*., GROW method to structure coaching interactions). A prime focus for the partner organisations and the research team has been ongoing sustainability of the interventions beyond the formal support of this project. This has necessitated the interventions be amenable to being ‘passed on’ to in-service champions in a train-the-trainer model, for example.

There is risk of data loss due to the multiple time points and staff turnover rates within the mental health field. Turnover of staff in mental health service organisations is up to 26% per annum [55]. These risks are being managed by allocation of a designated project coordinator within the research team, who will provide day-to-day liaison with the industry partners and take oversight of the intervention schedules and data collection. Each industry partner will identify a liaison officer who will have carriage of the coordination and scheduling responsibilities within their organisation. Our relatively large sample size anticipated for time pointone has been estimated with consideration given to the aforementioned industry attrition rate.

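### FIML would be better supported if intention to leave, job satisfaction and burnout, already collected but assigned only to other hypotheses, entered the missing-data model as auxiliary variables

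*Protocol article*

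**What the plan says.** Under Methods, Data analysis, one missing-data method is named: "We will deal with missing data using full-information-maximum-likelihood estimation (FIML"). It is preferred to list-wise or pair-wise deletion because it "uses all the available information for parameter estimation". The models described there relate condition (X) to transfer (Y), directly and through process variables (M) such as autonomy.

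Under Measures and data: "The battery of measures will also include measures of intention to leave [48] job satisfaction [49], and burnout [50"]. The next sentence gives their purpose: "This additional data will be utilised by the research team to explore another set of hypotheses distinct from those being investigated here". The questionnaires that serve the present hypotheses are then listed separately.

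Under Data collection and handling: "The study will last 18 months with data collection at multiple times points", and "Primary data comprises a questionnaire battery completed by participants at five time points throughout the intervention".

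Under Discussion, Anticipated challenges, data loss is attributed to the repeated time points and to turnover: "Turnover of staff in mental health service organisations is up to 26% per annum [55"]. The responses given are a project coordinator, liaison officers and a starting sample chosen with attrition in mind.

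**The concern.** FIML corrects for loss only as far as the variables in the fitted model explain it. Suppose a variable outside the model predicts leaving and also predicts the outcome, given what is already modelled. Then missing-at-random fails for that model, and the estimates describe a population tilted towards stayers. Intention to leave is an obvious candidate for such a variable, and job satisfaction and burnout are plausible ones. All three are in hand, yet the models as described do not include them.

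The measures taken against turnover protect the number of participants. They do not correct for a difference between leavers and stayers. If the less motivated staff leave, follow-up means of autonomy, attitude and knowledge are too favourable. This bears most on two planned analyses: overall effects in the entire sample, and the comparison of pre-post effect sizes with the earlier study (STARS 0.25, RKI 0.52), where only a small increase is expected. The arm comparison is affected only if the selection differs by arm.

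**Working it through.** The plan gives no figure for this point, so there is none to reproduce.

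**Inputs from the protocol.** Starting sample 200 ("We are anticipating a sample size of 200 at time point one"); 100 used for power; turnover at most 26% a year; study length 18 months; STARS comparator 0.25.

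**Step 1: possible loss.** With the upper turnover figure taken as constant:
- 12 months: 200 × 0.74 = 148 remain (26% lost).
- 18 months: 200 × 0.74^1.5 = 127 remain (36% lost).

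Both exceed 100, so numbers are covered and only bias is in question.

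**Step 2: bias with and without the auxiliary.** Large-sample simulation, all outcomes in SD units. For an outcome missing at follow-up with baseline complete, maximum likelihood amounts to regressing the outcome on the model variables among stayers and averaging the predictions over everyone. This was done with condition and baseline outcome only, and again with one auxiliary standing for intention to leave.

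Assumptions, none of them in the protocol: baseline–outcome correlation 0.5; baseline–auxiliary correlation −0.3; odds ratio (OR) for leaving 2 or 3 per SD of the auxiliary; partial correlation of auxiliary and outcome (given baseline) 0, 0.2 or 0.4 in size, negative in direction; arm effect 0.3.

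Bias in the whole-sample follow-up mean without the auxiliary, equal loss in both arms:

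| Partial correlation | Loss 26%, OR 2 | Loss 26%, OR 3 | Loss 36%, OR 2 | Loss 36%, OR 3 |
|---|---|---|---|---|
| 0 | 0.00 | 0.00 | 0.00 | 0.00 |
| 0.2 | 0.03 | 0.04 | 0.04 | 0.05 |
| 0.4 | 0.05 | 0.08 | 0.08 | 0.11 |

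Baseline is complete in this set-up, so the bias in the follow-up mean is also the bias in pre-post change. With the auxiliary in the model, every entry is within 0.002 of zero.

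**Step 3: bias in the arm comparison.**
- Equal loss in both arms: within about 0.002 of zero.
- Loss 20% in the values arm and 32% in the implementation arm (assumed): −0.014 (OR 2) and −0.018 (OR 3) at partial correlation 0.2; −0.026 and −0.034 at 0.4; 0 at partial correlation 0. The sign is against the values arm because the arm that loses more keeps the more selected stayers.
- With the auxiliary: within 0.002 of zero.

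**Step 4: scale.** The like-for-like comparator for pre-post bias is the earlier pre-post STARS effect: 0.03/0.25 = 12% and 0.11/0.25 = 44%. This assumes a similar standardising SD. The protocol does not say which wave supplies the pre-post contrast. If it is an early one, loss is below 26% and the bias is smaller. The transfer indicators and file audits run to 12 months, where the 26% columns apply.

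**The case against.** The strongest reply is that nothing is excluded. Measures and data gives the three measures a substantive use and does not bar them from the missing-data model. An auxiliary variable is by nature one that is not part of the hypothesis under test, so that section is compatible with the fix. The analysis plan is not shown and may already list auxiliaries. This stands, and for that reason the point is an improvement and not an error. It does not remove the point: the three measures are in hand, and the models as described would not use them.

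Several stronger readings are tempting, and the document does not support them:

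- A reader might see a contradiction in the remark about FIML using all available information. In context it contrasts FIML with deletion. It does not claim that every collected variable enters the model.
- A reader might take turnover to be named as the main cause of loss. The text names it beside the multiple time points and ranks neither. The 26% is an upper figure for the field, not a forecast for this trial.
- A reader might infer a large distortion of the arm comparison. If intention to leave fully determined who left, the stayers' mean shift would be φ(z)/(1−q): 0.350 at 20% loss and 0.526 at 32%. The difference of 0.176, times an outcome correlation of 0.4 to 0.6, gives 0.07 to 0.11 SD. That calculation assumes perfect determination and gives no credit for baseline. With odds ratios of 2 to 3 and baseline in the model, the figure falls to about 0.01 to 0.04 SD. Setting it against the STARS value of 0.25 would also divide a between-arm bias by a pre-post effect.

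It is also true that the protocol gives no correlation of these measures with leaving or with any outcome. If the partial correlation is nil, nothing is gained.

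**Conclusion.** The point holds as a low-cost improvement to a stated analysis choice. The protocol names FIML, acknowledges turnover, and collects three plausible predictors of leaving that the described models would not use. Under the stated assumptions, omitting them biases whole-sample or pre-post means by about 0.03 to 0.11 SD. That is enough to matter when the benchmark is 0.25 and only slightly larger effects are expected. The values-versus-implementation contrast is little affected: about 0.01 to 0.04 SD if loss is 20% v 32%, and about 0 if loss is equal. The odds ratios, correlations and arm-specific losses are all assumptions, and the loss of 26% to 36% rests on the upper turnover figure. The document does not support calling this a contradiction or a serious threat to the arm comparison.

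**What to change.** State that time-one intention to leave, job satisfaction and burnout enter the FIML models for the questionnaire outcomes as auxiliary (saturated-correlates) variables. Add later observed values where the model stays stable. In this form they inform the missing values without becoming covariates or mediators, so the condition, process and transfer paths keep their meaning. Report turnover by arm.

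The data are already in the battery, so the cost is a few lines of model code and somewhat larger models. For a model with three variables (X, M, Y), three time-one auxiliaries add 3 means, 3 variances, 3 covariances among themselves and 3 × 3 = 9 with the model variables, 18 parameters in all. All five waves would mean 15 auxiliaries and 15 + 15 + 105 + 45 = 180 parameters. With about 200 staff in 22 sites that may not converge, so time-one values should come first.

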## Methods

### Study design and procedure

This research is informed by two previous projects undertaken by this research team, and parallels data collection time frames to enable comparisons of implementation following the addition of the new intervention component. This project is supported by an Australian Research Council grant (LP09900708), with financial and in-kind contributions by the industry partners. Partner organisations are five well-established community-managed organisations involved in the direct provision of services to individuals living with severe and recurrent mental illnesses in the community. The partner organisations will nominate a number of suitable worksites drawn from across their service base to participate in the intervention and research components. We anticipate access to teams across a number of Australian states and government areas, allowing us to compare and control for the effects of geographical variables. In total, approximately 200 mental health workers from across 22 sites will be randomised and referred for intervention.

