### Participants

Participants will be randomised by work-site to either the experimental (values) or control (implementation). Cluster-randomisation will be adopted to increase the feasibility of roll out in the organisational setting (*e*.*g*., consistency across what ‘change’ for individuals within a single worksite will look like) and minimise contamination across conditions (*i*.*e*., individual randomisation would likely lead to decreased fidelity to condition due to inevitable interactions between individual staff within teams). A computerised random integer program will be used to refer worksites to condition. Once randomised, staff from within sites will be referred for training and invited to consent to participate in the research process. Blinding will not be used at the participant or worksite level for pragmatic reasons (*i*.*e*., ongoing coaching will require condition-specific protocol) and to maximise fidelity (*i*.*e*., workers will consult with colleagues from worksites in the alternate condition during the course of duties and need to understand the importance of staying within assigned protocol). Information about previous exposure to the training (*i*.*e*., staff who have participated in some CRM training before time one) will be sought to allow screening prior to inclusion in the final data set. Staff who do not consent to participation in research but are within randomised sites will still participate in all intervention components to maximise the benefit of this project for the partners, to promote intervention fidelity within the workplace, and to allow all mental health workers access to contemporary evidence-based practices and techniques.

The intervention will be facilitated by our team and comprises both training (three days) and a 12-month coaching intervention. All teams will receive the same two days of training in the CRM [10]. On the third day of training, they will receive different training activities, according to the condition (values or implementation). In-service coaches (to be trained by our team) will conduct coaching. The in-service coaches will be supported with monthly, group-based coaching-support sessions facilitated by an appropriately skilled project member. Features of each intervention condition are as follows.

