### Data analysis

The intervention analyses will focus on two major questions: What aspects of Transfer does the values interventions positively influence? By what processes does the intervention work? We are primarily interested in investigating effects at the cluster-level, though will explore overall effects of the addition coaching-component on the entire sample and participant-level data in the qualitative processes described. The figure below presents a model of the analyses. Model A represents the total effect of values intervention versus control condition (implementation) (X) on Transfer (Y). Model B represents the direct effect of X on Y, and the indirect effect through the mediator (M), our psychological process variable (autonomy).

Model C is a multiple mediation model, and will allow us to test the extent that our intervention targets multiple process variables (*e*.*g*., value importance, value success, value commitment). Contemporary research in the area of autonomous motivation has begun to challenge the utility of aggregated measures as outlined above [*e*.*g*., 25]. Rather than being mutually exclusive or ‘either or’ constructs, it may be more relevant to investigate the particular elements of motivation as described on the continuum outlined above (Figure 2). This seems especially relevant in this case given the specific goals individuals are striving toward are not self-generated and occur in the workplace where ‘enjoyment’ is not necessarily a motivational force that is amenable or desirable as a target for change. So, we will also be able to test effects of various regulators (*i*.*e*., guilt, enjoyment, importance, fun) on the outcome variable. We will use the bootstrapping method described by Preacher and Hayes [53] to test the meditational models.

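### Worksites are randomised within organisation, but the methods named for the mediation and predictor analyses carry no site level, so errors for the condition effect and the condition-to-mediator path would be understated

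*Protocol article*

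**What the plan says.** **Design.** The Abstract (Methods) describes cluster randomisation by worksite within each of five organisations. The Participants section confirms allocation by worksite and justifies it partly by the interactions among staff in a team. Study design and procedure gives the size: "approximately 200 mental health workers from across 22 sites will be randomised and referred for intervention".

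**Aim.** The Data analysis section says "We are primarily interested in investigating effects at the cluster-level". It defines Model A as the total effect of condition on transfer, Model B as adding autonomy as mediator, and Model C as adding several mediators.

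**Named methods.** For the mediation models the text begins "We will use the bootstrapping method described by" and cites a methods reference, without saying whether workers or sites are resampled. For predictors it says "Standard multiple regression analysis will test for predictors of transfer". Full-information maximum likelihood is named only for missing data.

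**Power.** The authors expect 200 workers but "have allowed for a more modest sample size of 100 in calculating power analyses". A Z test for proportions then gives a requirement of 48 of 100 participants, set against 37% in the previous study.

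**The concern.** Condition is constant within a site, so there are only 22 independent units for estimating its effect. If workers in the same site resemble each other, a method that counts each worker as independent understates the error of anything that contrasts conditions. The authors' own reason for randomising sites, that team members influence one another, is a reason to expect such resemblance.

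The stated aim (cluster level) and the named methods (no site level) therefore do not match. The section poses two major questions: which aspects of transfer the values intervention improves, and by what process. Model A answers the first, and the condition-to-mediator path is needed for the second. In both, chance differences among a few sites could be read as values effects or mediated effects.

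**Working it through.** **Inputs from the article:** 22 sites; 200 workers, so m = 200/22 = 9.09 per site; 100 workers in the power statement, so m = 100/22 = 4.55; five organisations; 37% reference rate; p<0.01. **Assumed, because the article is silent:** ICC 0.01 to 0.20; equal site sizes; 11 sites per arm; organisations of 4, 4, 4, 4 and 6 sites; share f of the ICC lying between organisations equal to 0, 0.5 or 0.8.

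**Step 1. The plan's own figure.** One-sample Z test, one-sided 0.01, independent workers: 100 × (0.37 + 2.326 × √(0.37 × 0.63/100)) = 48.23. This is the stated 48 to the nearest whole number (49 if the threshold must strictly be passed). It is recovered with a design effect of 1, so nothing was allowed for sites. Multiplying the variance by DE = 1 + (4.55 − 1) × ICC moves the threshold to 49.2 at ICC 0.05 and 50.1 at 0.10.

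**Step 2. Arm test, all correlation at site level (f = 0).** DE = 1 + (m − 1) × ICC; true level of a nominal two-sided 5% test = 2 × (1 − Φ(1.96/√DE)). Example at ICC 0.05: DE = 1 + 8.09 × 0.05 = 1.40, √DE = 1.19, level 9.8%.

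| ICC | DE, 200 workers | SE ratio | Effective N | True level, 200 workers | True level, 100 workers |
|---|---|---|---|---|---|
| 0.01 | 1.08 | 1.04 | 185 | 5.9% | 5.4% |
| 0.05 | 1.40 | 1.19 | 142 | 9.8% | 7.1% |
| 0.10 | 1.81 | 1.34 | 111 | 14.5% | 9.2% |
| 0.20 | 2.62 | 1.62 | 76 | 22.6% | 13.4% |

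Simulating ordinary regression on arm (22 sites of 9, 20,000 runs) gave 6.0%, 9.7%, 14.4% and 22.6%.

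**Step 3. Randomisation within organisation.** Organisation differences balance across arms, so only the site part inflates the arm contrast. With m = 9 the variance ratio is approximately (1 − ICC) + 9 × ICC × (1 − f). Example at ICC 0.10, f = 0.5: 0.90 + 0.45 = 1.35, level 9.2%.

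| ICC | f = 0 | f = 0.5 | f = 0.8 |
|---|---|---|---|
| 0.01 | 5.9% | 5.4% | 5.1% |
| 0.05 | 9.8% | 7.1% | 5.5% |
| 0.10 | 14.5% | 9.2% | 5.9% |
| 0.20 | 22.6% | 13.3% | 6.9% |

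(The f = 0 column repeats Step 2.) Simulation with balanced allocation inside the five assumed organisations agreed to within a percentage point or so. The ratio falls below 1 only if f exceeds 1 − 1/9 = 0.89.

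In the same simulations a t test on site means held about 5% at f = 0. With f at 0.5 or 0.8 and ICC 0.05 to 0.20 it fell to about 1% to 4%, because it ignores organisation. Adjusting the site means for organisation brought it back to about 5%.

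**Step 4. Indirect effect.** With no true condition-to-mediator path, a mediator-to-outcome slope of 0.5, f = 0 and workers resampled individually (1,500 runs of 500 resamples), a nominal 5% bootstrap rejected in 4.9% at ICC 0, and in 10.5%, 15.7% and 22.5% at ICC 0.05, 0.10 and 0.20.

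**The case against.** The best defence is that this is a condensed article which declares a cluster-level interest, so the site-aware method may sit in a fuller plan. That stands in part. No estimator is named for Model A, and nothing says what unit the bootstrap resamples. A reader might infer that the plan fixes a worker-level test for every arm comparison; the text does not go that far. But a declared interest is not a method, the methods that are named have no site level, and the word standard for the regression points away from one.

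Three further points limit the concern:

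- The regression sentence is about predictors of transfer. Many of these, such as autonomy or attitudes, vary within sites and are affected less than condition. The error rates above belong to the condition contrast.
- A reader might count the Z test as a third faulty arm test. It compares the previous study with the present one, so it cannot turn site differences into values effects. Its threshold merely omits clustering.
- A reader might take 10% to 23% as the expected error rate. Those figures require an ICC of 0.05 or more with none of it between organisations. The Abstract's randomisation within organisation makes them an upper case.

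**Conclusion.** The point holds in this form: sites are randomised and the stated interest is at cluster level, but the bootstrap and the regression are specified without a site level, and no cluster adjustment appears anywhere in the article. Applied as written, they understate the error of the condition effect and of the condition-to-mediator path.

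The size is uncertain. For 200 workers in 22 sites a nominal 5% arm test runs at about 5% to 23% over an ICC of 0.01 to 0.20 and an organisation share of 0 to 80%, all assumed. At ICC 0.01 the effect is slight; at 0.10 with half the correlation between organisations it is about 9%. The direction is firm unless nearly all the correlation lies between organisations. The bootstrap figures also assume that individual workers are resampled, which the article neither states nor rules out.

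**What to change.** - Replace the single-level regression with a model that has a random intercept for site and organisation as a fixed stratum, a logistic link where transfer is binary, and small-sample degrees of freedom based on the number of sites. An equivalent site-level analysis adjusted for organisation would also serve; plain site means without organisation would be conservative if organisations differ.
- State the estimator for Model A, and test Models A to C with condition at site level, using multilevel mediation or another method that respects sites. Say explicitly that individual workers are not resampled.
- Bring the cluster-level aim and the named methods into agreement in the Data analysis section, and state an assumed ICC and design effect beside the 48-of-100 threshold.

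The cost is revised wording, a little more programming and intervals that are wider but correct. No new data are needed.

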### Implementation condition

The delivery of the implementation condition intervention components follow the same format as in the values condition but differ in focus and content. The day three of training in the implementation group is experiential in nature, but focuses on addressing opportunities for and barriers to the implementation of the CRM into practice within the workplace. The methodology used to structure and support the implementation intervention is the ‘Strengths, Weaknesses, Opportunities, and Threats (SWOT) Analysis’ developed by Albert Humphrey and used extensively in organisational contexts [43,44].

Coaching in the control condition is consistent in format and overall structure to the values condition. Implementation coaching adopts an alternate focus on identification and resolution of issues related to implementation of CRM in the workplace as identified by participants. For example, pragmatic issues (*e*.*g*., addressing technical issues associated with new practices) or attitudinal issues (*e*.*g*., working through resistance to change from clients or colleagues).

The aims of the implementation condition are as follows:

1. Ongoing exposure to and skills-based practice with the CRM.

2. Opportunity to identify and develop strategies to address factors that are impeding implementation (*e*.*g*., resistance from clients or co-workers).

3. Regular and sustained investment (12 x 1 month coaching sessions) in the professional and personal development of staff using CRM tools as the framework.

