In both conditions, participants are using the same protocol and model of practice they are to use with their clients upon implementation. Coaching therefore promotes experiential learning [45] in both conditions. We expect this will result in increased transfer of CRM into practice compared to our previous research. In the values condition there is an additional parallel process such that mental health staff will be actively encouraged to work with the CRM practices in relation to their own lives and values, just as their clients would. That is, they are applying both the practices and the underlying processes ‘for real’ (values), rather than just practising in the use of the CRM (implementation). The value of parallel relationships in transferring knowledge from one dyad (*e*.*g*., supervisor and clinician) to another (*e*.*g*., clinician and client) has been elaborated within counselling literature [46]. We hypothesise this additional parallel relationship will increase implementation as a result of enhanced sense of meaning and connection with the CRM such that it becomes more internalised [47].

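### The only power calculation shown compares the present sample with an earlier study and credits the expected gain to the values intervention, so it says nothing about values versus implementation

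*Protocol article*

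**What the plan says.** All references are to the Protocol article.

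- **Data analysis (power statement).** The reference rate comes from earlier work by the same team: "In our previous study, we found 37% of people transferred training". The sample is a reduced figure: "We are anticipating a sample size of 200 at time point one, but have allowed for a more modest sample size of 100". The target is then that "we need at least 48 out of the 100 participants to obtain a significant difference at p<0.01 to detect a 10% increase in transfer", and the comparison is described as made "in order to show a significant increase in the proportions between the former and present studies". It closes with: "We believe this difference is very achievable with the addition of the values-focused interventions".
- **Implementation condition.** Controls have their own third training day and 12 monthly coaching sessions: "Coaching in the control condition is consistent in format and overall structure to the values condition". After noting that coaching promotes experiential learning in both conditions, the section adds: "We expect this will result in increased transfer of CRM into practice compared to our previous research".
- **Data analysis (models).** Model A is the total effect of values versus implementation on transfer, with main interest at cluster level. The same paragraph plans to explore, in the entire sample, the overall effect of the added coaching.
- **Study design and procedure; Participants.** About 200 workers from 22 sites are randomised by worksite to the two conditions. No allocation ratio is given.

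**The concern.** The power statement and the design point in different directions. The question that randomisation can answer is whether values content adds to transfer beyond implementation content. The calculation addresses another question: whether the present participants exceed a rate seen in an earlier study. The article itself expects that rate to be exceeded through coaching in both conditions. A gain over 37% is thus predicted even if values content adds nothing, but the power paragraph links it to the values interventions.

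Two things are at stake. A rise over 37% has a ready-made explanation in terms of values that the comparison cannot support. And a reader may take the difference described as readily achievable as a guide to what the randomised comparison can show, which it is not.

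**Working it through.** **Inputs from the article:** historical rate 37%; 100 participants for power, 200 anticipated; threshold 48 of 100 at p<0.01; 22 sites. **Assumed:** 1:1 allocation, equal site sizes, 100 and 200 as totals over both conditions, ICC of 0, 0.05 and 0.10, two-sided alpha 0.05, control rate 37%.

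**1. Reproducing the threshold.** One-sample Z test against a fixed 37%, one-sided 0.01:

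0.37 + 2.326 × √(0.37 × 0.63 / 100) = 0.37 + 2.326 × 0.0483 = 0.482

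This is about 48 of 100, so the figure is recovered approximately. Exactly 48 gives z = 0.11/0.0483 = 2.28, p = 0.011 one-sided and 0.023 two-sided; the first counts below 0.01 are 49 and 50. What matters here is the form of the test: 37% enters as a known constant, and no concurrent control group enters at all.

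**2. Does meeting the target say anything about values?** With 50 per condition, 24/50 and 24/50 give 48/100 and a randomised difference of zero. Conversely, if controls stayed at 37%, the values arm would need 2 × 48% − 37% = 59% for the pooled rate to reach 48%. The same pooled result fits no values effect or a 22-point effect.

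**3. What the randomised contrast could detect.** Design effect = 1 + (m − 1) × ICC, where m is participants per site (100/22 = 4.55; 200/22 = 9.09). Effective n per arm = (N/2) / design effect. Power is for the two-proportion Z test with pooled variance under the null.

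| N | ICC | Design effect | Effective n per arm | Detectable difference from 37%, 80% power | Power for 37% v 47% |
|---|---|---|---|---|---|
| 100 | 0 | 1.00 | 50.0 | 28 points | 17% |
| 100 | 0.05 | 1.18 | 42.5 | 30 points | 15% |
| 100 | 0.10 | 1.36 | 36.9 | 32 points | 14% |
| 200 | 0 | 1.00 | 100.0 | 20 points | 30% |
| 200 | 0.05 | 1.41 | 71.2 | 23 points | 23% |
| 200 | 0.10 | 1.81 | 55.3 | 26 points | 18% |

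**4. Sensitivity to the control rate.** The article expects controls to exceed 37%. Repeating step 3 from a 48% control rate gives detectable differences of 27, 29 and 31 points (N=100) and 20, 23 and 26 points (N=200), with power for a 10-point difference of 13–17% and 18–29%. The choice of control rate hardly matters.

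**The case against.** The strongest reply is that the article already puts the values inference in the right place. Model A is the randomised contrast, and the whole-sample effect is treated separately, as exploratory and due to coaching. Comparison with the team's earlier projects is an open design purpose. On this view the closing sentence of the power paragraph is a remark on feasibility, not a rule of inference. That stands in part. A reader might infer that the trial will draw its conclusion about values from the historical comparison; the document does not support this. The power paragraph remains at odds with the rest of the article, because it links to values a gain that other sections attribute to coaching.

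Four more limits stand:

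- **Origin of the 200.** A reader might infer that the sample size was derived from this calculation. It was not: the Anticipated challenges section ties the 200 to staff turnover.
- **Meaning of the 10%.** It is stated as a difference between studies, never between arms. The low power for a 10-point randomised difference is an illustration, not a refutation of a claim made.
- **Composition of the 100.** Neither the split nor who makes up the 100 is stated. If the 100 were the values arm alone, the comparison would still be historical and would still mix values content with coaching.
- **Scope.** The figures concern one binary measure. Transfer is also assessed by time to implementation, care-plan audit, ratings and self-report.

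The Abstract mentions a third day and coaching only for the experimental group. The Methods sections are explicit that both conditions have them, and I rely on those.

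Finally, a condensed article may leave a between-arm power calculation to a fuller document. Its absence alone is not the point; the printed calculation answers another question and carries the wrong attribution.

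**Conclusion.** The point holds in this limited form. The printed calculation tests present participants against a fixed 37% and credits the expected gain to the values interventions, although the article expects coaching in both conditions to produce such a gain. Reaching 48 of 100 would not be evidence for the values component, and the calculation does not inform Model A. The planned randomised analysis is untouched.

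The conclusion about attribution needs no assumed figure. The size does: under the assumptions listed in the working, the randomised contrast could detect roughly 28–32 points with 100 analysed or 20–26 with 200, and a 10-point between-arm difference would have 14–17% or 18–30% power. Even with no clustering and all 200 retained, power for 10 points is only 30%, so the message does not depend on the ICC.

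**What to change.** Change text only, in Data analysis:

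1. Label the comparison with the earlier study, both the 37% transfer rate and the pre-post effect sizes for STARS and RKI, as descriptive of the whole package of training and coaching. Delete or reword the sentence that credits the gain to the values-focused interventions.
2. State that inference about values rests on the randomised contrast between values and implementation. Give the cluster-adjusted detectable difference for work-sample transfer at N=100 and N=200, with the allocation ratio, control rate, ICC range and alpha used.

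No extra enrolment or data collection is asked for. The cost is that the stated sensitivity becomes less favourable than the present paragraph suggests.
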